### Data collecting and follow-up

According to the protocol, assessments will be repeated 7 times during the 12 weeks intervention: at baseline, at 2 weeks, at 4 weeks, at 6 weeks, at 8 weeks, at 10 weeks, and at 12 weeks. For those patients who have been induced to remission at the end of the intervention, we will follow up for 24 weeks. After enrollment, participants will attend a total of thirteen trial visits. Participants who completed our trial will be provided with 400 RMB for transport compensation. At the beginning and the end of the study, Mayo score, colonoscopy, mucosal histology, heath-related quality of life, biochemical parameters, and safety index will be measured. However, partial Mayo score, symptom indicators (e.g., diarrhea, bloody stools, and abdominal pain), biochemical parameters (e.g., fecal calprotectin, hypersensitive-C reactive protein, erythrocyte sedimentation rate, stool routine, occult blood test), and safety index (e.g., blood routine, liver function and kidney function) will be evaluated at 2 weeks, 4 weeks, 6 weeks, 8 weeks, and 10 weeks respectively.

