### Termination criteria

Patients will be terminated if they meet the following criteria:
Abnormality of safety index during treatment (ALT more than twice the upper limit of normal, Cr more than the upper limit of normal, platelet count less than 50 × 109/L, white blood cells less than 3.0 × 109/L)Worse condition during the course (bloody stools more than 6 times daily accompanied by body temperature > 37.8 °C or Hb < 10.5 g/dL)

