### Statistical analysis

According to our protocol, all data analyses will be conducted based on pre-established statistical analysis plan. All analyses of data will be performed by SAS software (v. 9.3; SAS Institute Inc., Cary, NC, USA). To ensure the consistency and reliability of the conclusions, both intention-to-treat (ITT) analysis and per-protocol (PP) analysis will be done if necessary. All missing data will be imputed by multiple imputation. Statistical description will be performed with frequency, mean, median, standard deviation, lower quartile (P25), upper quartile (P75), minimum, and maximum. Normality of all quantitative (continuous) variables (e.g., demographic characteristics, vital signs, biochemical parameters) will be tested by the Kolmogorov-Smirnov test. For normal distribution data, independent sample *t* test and paired sample *t* test will be employed to compare parameters at the beginning and the end of the study between and within groups, respectively. For abnormal distributions data (e.g., quality of life, inflammation markers), the Mann-Whitney *U* test and Wilcoxon signed-rank test will be used instead. For qualitative (categorical) variables, the chi-square test or Fisher’s exact test will be used, such as clinical response rate, endoscopic response rate, and mucosal healing rate. In the evaluation of efficacy and analysis of influencing factors, center and disease will be used as covariates. Covariance analysis (ANCOVA) will be used [35]. Multiple linear regression or logistic regression will be used to analyze the influencing factors and evaluate the effect of gender and condition on the efficacy of the two groups. For all analyses, *P* < 0.05 will be considered statistically significant.

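### Calprotectin, hs-CRP, ESR and partial Mayo are measured at up to seven visits but tested only at start and end without baseline adjustment; a baseline-adjusted repeated-measures model would be more precise at no data cost.

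*Protocol article*

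**What the plan says.** Three parts of the Protocol article bear on this.

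- **Collection.** Data collecting and follow-up schedules the full set of measurements twice, in the sentence that opens "At the beginning and the end of the study, Mayo score, colonoscopy, mucosal histology, heath-related quality of life, biochemical parameters, and safety index will be". Between those two points come partial Mayo score, symptoms, safety indices and "biochemical parameters (e.g., fecal calprotectin, hypersensitive-C reactive protein, erythrocyte sedimentation rate, stool routine, occult blood test"; the section says that these "will be evaluated at 2 weeks, 4 weeks, 6 weeks, 8 weeks, and 10 weeks respectively". Outcomes lists calprotectin, hs-CRP and ESR among the secondary outcomes. Partial Mayo is not listed there.
- **Analysis.** Statistical analysis says that the independent and paired t tests "will be employed to compare parameters at the beginning and the end of the study between and within groups, respectively". Mann-Whitney and Wilcoxon tests replace them for skewed data, with inflammation markers given as an example. For the adjusted analysis, "center and disease will be used as covariates". No repeated-measures model is named, and the outcome's own baseline value is not named as a covariate.
- **Missing data.** The same section says "All missing data will be imputed by multiple imputation". It does not list the variables of the imputation model. It refers to a pre-established analysis plan, which is not at hand.

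**The concern.** Three secondary outcomes are measured at baseline and weeks 2, 4, 6, 8, 10 and 12, but the named tests use at most the first and last of these seven values. The section states its tests and their time points, so this is a choice and not a silence. An unadjusted comparison of end values discards the correlation between a patient's baseline and week-12 values, and it discards the interim values of patients who lack week 12. At stake is precision on secondary outcomes in a trial of 120 patients.

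Dropout is a second, lesser matter. Termination criteria include "Worse condition during the course (bloody stools more than 6 times daily accompanied by body temperature" above a threshold or low haemoglobin, so some missing week-12 values may follow symptoms that the interim visits recorded. Interim values would then be useful in the imputation of week-12 response.

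**Working it through.** **Which variables qualify**

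- Measured at baseline, at weeks 2 to 10 and at week 12: calprotectin, hs-CRP, ESR, and partial Mayo (obtainable from the full Mayo score at the two ends).
- Listed only at the beginning and end: total Mayo, colonoscopy and quality of life (IBDQ). The primary response and both endoscopic outcomes therefore have no interim values of their own.
- TNF-α is not in the interim list.

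**Assumptions.** The document gives no correlations. I assume a correlation of 0.4 + 0.6 × φ^lag, with lag counted in two-week visits and φ = 0.6 or 0.8.

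- Baseline to week 12 (lag 6): 0.4 + 0.6 × 0.047 = 0.43 and 0.4 + 0.6 × 0.262 = 0.56.
- Week 10 to week 12 (lag 1): 0.76 and 0.88.
- Week 2 to week 12 (lag 5): 0.45 and 0.60. Early leavers contribute only these weaker values.

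**Step 1, baseline adjustment.** The variance of a baseline-adjusted comparison relative to a t test of end values is 1 − r².

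- r = 0.43: 1 − 0.183 = 0.817, a cut of 18%.
- r = 0.56: 1 − 0.310 = 0.690, a cut of 31%.
- Wider range: r = 0.3 gives 0.91 and r = 0.7 gives 0.51.

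If the t test were applied to change from baseline, the ratio is (1 − r²) / [2(1 − r)] = (1 + r)/2, which is 0.71 and 0.78. The gain is still 22% to 29%.

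**Step 2, interim visits.** I simulated 60,000 patients per arm with seven visits at 10% and 20% dropout, missing completely at random for this part. The variance of the repeated-measures model relative to a completers' ANCOVA was 0.93 to 0.98, that is 2% to 7% less. In standard error this is 1 − √0.98 = 1.0% to 1 − √0.93 = 3.6%.

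A closed-form check takes the variance of a week-12 mean relative to completers only as 1 − d × ρ², with d the dropout and ρ the correlation of the interim with the week-12 value. At d = 10% the standard error falls by 0.5% (ρ = 0.3), 1.3% (0.5), 2.5% (0.7) or 4.1% (0.9). At d = 20% it falls by 0.9% to 8.5%. The interim gain is small either way.

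**Step 3, together.** 0.817 × 0.98 = 0.80 and 0.690 × 0.93 = 0.64, which agrees with the simulated ratio of 0.64 to 0.80. Total variance falls by 20% to 36%, so intervals are 1 − √0.80 = 11% to 1 − √0.64 = 20% shorter.

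**Step 4, the imputation.** If it used baseline only and dropout followed the last observed severity, the same simulation at true rates of 79% and 41% gives these response differences:

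| Data used | Difference |
|---|---|
| Full data | 0.382 to 0.386 |
| Imputation from baseline only | 0.368 to 0.382 |
| Imputation with interim visits | 0.381 to 0.386 |

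The error is about 0.3 to 1.5 points, towards a smaller effect. With 60 per arm, the standard error of the difference is √[(0.79 × 0.21 + 0.41 × 0.59)/60] = √(0.4078/60) = 8.2 points, so the worst case is 1.5/8.2 = 0.18 standard errors. In a separate continuous example (true difference 0.5 SD, dropout 6.5% and 11.6%), baseline-only imputation gave 0.472 and imputation with the interim value 0.503, with standard errors of 0.184 and 0.186.

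**The case against.** The strongest reply is that the article defers to an analysis plan that is not shown, and that a week-12 comparison of secondary markers is legitimate. Interim visits also serve safety monitoring. ANCOVA is already named, and "disease" as a covariate might mean baseline severity. The Abstract says that variables will be assessed at every visit under intention to treat.

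Part of this stands. The named tests are valid, so the point concerns efficiency and not error. But the Abstract describes assessment and not analysis, and the section itself fixes tests and time points for continuous data. Whatever "disease" means, it is not stated to be each marker's own baseline value.

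A reader might infer more: that interim data are left out altogether, so that week-12 response is overstated and the primary comparison biased. The document does not support that.

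- All missing data are to be multiply imputed, and nothing restricts the imputation to baseline. Its contents are ordinary analysis-plan detail.
- Dropout criteria promise follow-up of patients who discontinue and an effort to complete their assessments, so termination does not automatically mean a missing week-12 value.
- Some termination rules are laboratory thresholds and not symptoms.
- The figures in Step 4 describe a baseline-only plan that the article never states. Even then the error is small and runs against the new treatment.

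A reader might also credit the interim visits with the whole 20% to 36% gain. Most of it is baseline adjustment.

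**Conclusion.** The point holds as a free improvement affecting secondary outcomes. For calprotectin, hs-CRP, ESR and partial Mayo, the named start-and-end tests are less precise than a baseline-adjusted repeated-measures model on the same data. The gain is a variance roughly 20% to 36% lower than with an end-value t test, of which 18% to 31% is baseline adjustment. The interim visits reduce the remaining variance by a further 2% to 7%. These sizes rest on assumed baseline to week-12 correlations of 0.43 to 0.56 and dropout of 10% to 20%; the article plans for 10% and gives no correlations. No bias in the primary result is established.

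**What to change.** In Statistical analysis:

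1. Analyse calprotectin, hs-CRP, ESR and partial Mayo with a mixed model for repeated measures, with arm by visit, baseline by visit and site as terms, and skewed markers on the log scale. Report the week-12 contrast between arms as the single comparison for each variable. Six post-baseline visits give 6 × 7/2 = 21 parameters in an unstructured covariance matrix, so name a simpler fallback in case of non-convergence.
2. Analyse IBDQ by ANCOVA with its baseline value and site. Treat TNF-α the same way if it has no interim measurements.
3. As a minor addition, state that a short set of interim values enters the multiple imputation of week-12 response, for example partial Mayo by visit, by arm. Keep it short. Three partial Mayo components plus two markers at five visits would be 5 × 5 = 25 variables against about 60 × 0.9 = 54 completers per arm, which is too many.

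The cost is wording and programming. No visits, samples or patients are added. Trial status says that enrolment is still open, so the change can be fixed before unblinding.

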### Data management and quality control

To ensure the quality of this trial, an external monitoring agency (a CRO located in Nanjing) will be hired to help data collection, management, and analysis across all subcenters. All data will be recorded (double-entered) on electronic case report forms (eCRFs) by trained investigators and will be monitored monthly via electronic data capture system. For each abnormal or missing datum, a query will be automatically sent to the investigator. Once all the inconsistencies or queries are solved, the database will be locked for statistical analysis.

### Statistical analysis

According to our protocol, all data analyses will be conducted based on pre-established statistical analysis plan. All analyses of data will be performed by SAS software (v. 9.3; SAS Institute Inc., Cary, NC, USA). To ensure the consistency and reliability of the conclusions, both intention-to-treat (ITT) analysis and per-protocol (PP) analysis will be done if necessary. All missing data will be imputed by multiple imputation. Statistical description will be performed with frequency, mean, median, standard deviation, lower quartile (P25), upper quartile (P75), minimum, and maximum. Normality of all quantitative (continuous) variables (e.g., demographic characteristics, vital signs, biochemical parameters) will be tested by the Kolmogorov-Smirnov test. For normal distribution data, independent sample *t* test and paired sample *t* test will be employed to compare parameters at the beginning and the end of the study between and within groups, respectively. For abnormal distributions data (e.g., quality of life, inflammation markers), the Mann-Whitney *U* test and Wilcoxon signed-rank test will be used instead. For qualitative (categorical) variables, the chi-square test or Fisher’s exact test will be used, such as clinical response rate, endoscopic response rate, and mucosal healing rate. In the evaluation of efficacy and analysis of influencing factors, center and disease will be used as covariates. Covariance analysis (ANCOVA) will be used [35]. Multiple linear regression or logistic regression will be used to analyze the influencing factors and evaluate the effect of gender and condition on the efficacy of the two groups. For all analyses, *P* < 0.05 will be considered statistically significant.

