### Sample size and power calculation

The sample size was calculated according to the primary outcome (clinical response rate) at 12 weeks after initiation. The sample size calculation was based on the comparison of the proportions in the QCHS granule group versus the placebo group. On the basis of previous study and clinical experience, we predicted that the clinical remission rates at 12 weeks would be 79% in the QCHS granule group and 41% in the placebo group [27, 28]. A difference of 10% was selected as the smallest difference that would be of clinical significance. For a two-sided significance level of 0.05 (*α* = 0.05), it is estimated that a sample size of 54 subjects per group will be required to detect the superiority of QCHS granule over placebo with a test power of 80%. Under the hypothesis that some patients are unable to follow-up or unsuitable for analysis, the sample size will be inflated. Considering 10% drop out, the total planned sample size will be 60 per group.

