### Withdrawal criteria

Patients who *do not* meet the inclusion criteria, have no data after randomization, have never used research medication, and take forbidden drugs will be withdrawn from this study.

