### Dropout criteria

Patients who are unable to be followed-up after informed consent and randomization will be considered dropout of our study.

Those patients who discontinue will be followed up for detailed reports throughout the study. We will try our best to contact subjects, record reasons, and complete assessment. Those patients who suffer an adverse event will be treated according to clinical practice guidelines. All the data of the research process will be recorded timely and accurately.

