### Outcomes

The primary outcome of this study is the clinical response rate in patients with moderately active UC. The clinical response refers to a decrease (from the baseline) of the total Mayo score by at least 30% (or 3 points) together with a decrease of the rectal bleeding subscore by at least 1 point (or rectal bleeding subscore of 0 or 1 point) with no individual subscore exceeding 1 point [32].

The secondary outcomes are as follows: health-related quality of life measured by the Inflammatory Bowel Disease Questionnaire (IBDQ) [33], endoscopic response rate defined as a decrease of Mayo disease activity index endoscopy subscore by at least 1 [32], mucosal healing rate defined as endoscopy subscore of Mayo disease activity index of 0 or 1, and improvements in inflammatory markers (e.g., fecal calprotectin, tumor necrosis factor-α and hypersensitive-C reactive protein, erythrocyte sedimentation rate) [34].

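### Multiple imputation of all missing data, whatever the reason, gives patients terminated for worsening disease a chance of being scored as responders

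*Protocol article*

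**What the plan says.** All references are to the protocol article.

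- **Statistical analysis:** "All missing data will be imputed by multiple imputation". No reason for missingness is treated differently.
- **Termination criteria:** one ground is deterioration, "Worse condition during the course (bloody stools more than 6 times daily accompanied by body temperature" above 37.8 °C or haemoglobin below 10.5 g/dL). The other is "Abnormality of safety index during treatment", defined by laboratory limits.
- **Withdrawal criteria:** patients who "take forbidden drugs will be withdrawn from this study". The article does not define which drugs are meant.
- **Dropout criteria:** for those who discontinue, "We will try our best to contact subjects, record reasons, and complete assessment".
- **Outcomes:** "The clinical response refers to a decrease (from the baseline) of the total Mayo score by at least 30% (or 3 points"), together with a rectal bleeding condition. Nothing says how a terminated or withdrawn patient is scored.
- **Data collecting and follow-up:** "At the beginning and the end of the study, Mayo score, colonoscopy, mucosal histology" and other measures are taken. At weeks 2, 4, 6, 8 and 10 only the partial Mayo score is planned, so the end visit is read here as week 12.
- **Sample size and power calculation:** 12-week rates "would be 79% in the QCHS granule group and 41% in the placebo group", with 10% dropout allowed.

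**The concern.** The primary outcome needs a total Mayo score, which includes endoscopy. A patient stopped for worsening at week 4, say, has no such score after baseline unless an end assessment is obtained. If it is not, the stated rule sends that patient to multiple imputation.

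Standard multiple imputation assumes missing-at-random: given the observed data in the model, the patient's outcome is distributed like that of patients who were assessed, most of whom completed treatment. For a patient stopped because the disease got worse, the reason for the missing value is itself evidence of failure. Every draw that comes out as response credits the arm with a success that did not occur. The primary outcome is binary and the trial has 60 patients per arm, so a few such patients can move the estimated difference.

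**Working it through.** **Inputs from the plan.** Rates of 79% and 41%; 60 per arm; 10% dropout. The dropout step reproduces: 54 / (1 − 0.10) = 60. (The 54 itself does not reproduce at the stated 80% power: it comes to 25 per group with no margin, or 41 with a 10-point margin. That is a separate matter and nothing below depends on it.)

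**Assumptions for the illustration.** A share d of each arm stops early; every one of these patients is unassessed and a true failure; imputation uses the arm's observed rate r and ignores post-baseline data. Then:

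- stops counted as failures: arm rate = r(1 − d)
- imputed at the arm's rate: arm rate = r
- overstatement per arm = r·d

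**Balanced stopping, d = 10% in each arm.** The plan does not say whether 79% and 41% are rates with stops counted as failures or rates among those assessed, so both readings are shown.

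| Reading of 79% / 41% | Stops as failures | Imputed at arm's rate | Overstatement |
|---|---|---|---|
| Stops already counted as failures | 79.0 − 41.0 = 38.0 | 79/0.90 − 41/0.90 = 87.8 − 45.6 = 42.2 | 4.2 points |
| Rates among those assessed | 79 × 0.90 − 41 × 0.90 = 71.1 − 36.9 = 34.2 | 79.0 − 41.0 = 38.0 | 3.8 points |

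On the second reading, the failures credited as responders number 60 × 0.10 × 0.79 = 4.7 for QCHS and 60 × 0.10 × 0.41 = 2.5 for placebo.

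**A better-informed model.** Suppose the week 2 to 10 data lower the imputed probability for these patients to a fraction c of the arm's rate (second reading, d = 10%). The difference is 34.2 + c × 3.8:

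- c = 0.5: 36.1, overstated by 1.9
- c = 0.25: 35.15, overstated by 0.95

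**Unbalanced stopping.** These splits are assumptions; the plan gives none.

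- 15% QCHS, 5% placebo. First reading: 79/0.85 − 41/0.95 = 92.9 − 43.2 = 49.8 against 38 (+11.8). Second reading: 38 against 67.15 − 38.95 = 28.2 (+9.8).
- 5% QCHS, 15% placebo. First reading: 79/0.95 − 41/0.85 = 83.2 − 48.2 = 34.9 against 38 (−3.1). Second reading: 38 against 75.05 − 34.85 = 40.2 (−2.2).

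**No true effect, 41% in both arms.** With 10% stopping in each arm, both rates become 41/0.90 = 45.6%, and the difference is unbiased. With 15% against 5% they become 48.2% and 43.2%, and the chance of a false finding for QCHS rises from 2.5% to about 8%. This is a normal approximation that ignores between-imputation variance.

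**The case against.** The strongest reply is that stopping treatment is not the same as missing data. The Dropout criteria section says that patients who discontinue are followed up and that assessment is attempted. A terminated patient who attends at week 12 is scored on observed data and nothing is imputed. This stands as a limit on size: the documents do not show how often the assessment would be missing. It does not remove the problem, because only an attempt is promised.

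Second, the article gives no imputation model and refers to an analysis plan that is not shown. Leaving the model to that plan is normal. Partial Mayo score, symptoms, calprotectin and CRP are collected at weeks 2 to 10, and a patient who met the worsening rule would probably have poor recent values. A model using them would lower the imputed probability of response, though not to zero. The point here is the rule that is stated, which covers all missing data, and not the absence of detail.

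Three stronger readings are tempting, and the documents do not support them:

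- A reader might infer that everyone terminated or withdrawn is a known treatment failure. A laboratory safety termination is not shown to be non-response of the colitis; scoring it as failure is an estimand choice. Nor is there any evidence that such stops would concentrate in the herbal arm.
- A reader might infer that patients withdrawn for forbidden drugs are imputed. They are listed with those who fail the inclusion criteria, have no data or never took study drug, so withdrawal may mean removal from the analysis. That would be a different problem. The drugs are undefined, so their use is not shown to be rescue.
- A reader might infer a bias above the plan's 10-point smallest relevant difference. The 15%/5% split gives 11.8 points on one reading and 9.8 on the other, and the split is assumed.

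Non-responder scoring is also not the only defensible remedy. Reason-specific or delta-adjusted imputation could serve too.

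**Conclusion.** The point holds for termination due to clinical worsening. Followed as written, the plan gives an evident failure a positive probability of response whenever the week-12 assessment is missing. At the plan's own 10% allowance the overstatement is at most about 4 points when stopping is balanced. That figure rests on every stop being an unassessed true failure and on imputation at the arm's observed rate, and it shrinks towards 1 to 2 points if the model gives these patients a quarter to half of that rate. Larger bias, or bias against QCHS, needs unbalanced stopping that the documents do not predict. The actual size and direction are therefore unknown. This should be fixed, but the documents do not show that it threatens the trial's conclusion.

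**What to change.** In the analysis rules, before unblinding:

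1. For the primary and other binary outcomes, count patients terminated for clinical worsening before week 12 as non-responders.
2. State how safety-laboratory terminations and forbidden-drug withdrawals are scored, and keep both groups in the ITT set.
3. Restrict multiple imputation to outcomes missing for other reasons, with the week 2 to 10 partial Mayo scores in the model.
4. Add a sensitivity analysis in which every missing outcome counts as non-response.

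The cost is a few sentences and a few lines of code. Absolute response rates will look somewhat lower. No clinical procedure changes.

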## Methods

### Study design

This is a prospective, multicenter, randomized, double-blind, placebo-controlled, superiority clinical trial, which conforms to the Consolidated Standards of Reporting Trials (CONSORT) 2010 statement guidelines [24], the Standard Protocol Items: Recommendations for Interventional Trials (SPIRIT) 2013 Statement [25], and the Standard Protocol Items for Clinical Trials with Traditional Chinese Medicine: Recommendations, Explanation and Elaboration (SPIRIT-TCM) Extension 2018 Statement [26]. The study began in January 2016 and will last until October 2022. A total of 120 eligible patients will be enrolled and randomized into the QCHS granule group or the placebo group. All patients will voluntarily sign the informed consent prior to enrollment. Prior to allocation, each of them will be screened by the eligibility criteria. According to patients’ included sequence number equally, block randomization will be performed to ensure equal group sizes with an allocation of 1:1 (permuted block sizes of 6). Participants in the QCHS granule group will receive QCHS granule (125 g daily, orally) for continuous 12 weeks, while patients in the placebo group will receive QCHS granule placebo (125 g daily, orally) for the same duration. Both groups will be given basic treatment with mesalazine (5-aminosalicylic acid, 4 g/day). Researchers and patients will be blinded from the beginning of the trial. All interested outcomes including patient-reported outcomes will be collected before (0 weeks) and after intervention (2 weeks, 4 weeks, 6 weeks, 8 weeks, 10 weeks, and 12 weeks). The whole study period will last 36 weeks, including 24 weeks of follow-up. The complete SPIRIT (2013) checklist and SPIRIT-TCM (2018) checklist for the study are provided in Additional files 1 and 2. The overview and the SPIRIT schedule of the study are illustrated in Figs. 1 and 2, respectively.

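### For the continuous secondary outcomes the protocol gives two between-group analyses without ranking them, and neither names the outcome's own baseline value as a covariate

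*Protocol article*

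**What the plan says.** The Outcomes section of the protocol article lists, among the secondary outcomes, "health-related quality of life measured by the Inflammatory Bowel Disease Questionnaire (IBDQ" and four inflammatory markers: fecal calprotectin, TNF-α, hs-CRP and ESR.

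The Statistical analysis section then describes two routes for comparing the groups on continuous outcomes.

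- **Unadjusted tests.** Normality of every quantitative variable "will be tested by the Kolmogorov-Smirnov test". If the data pass, independent and paired t tests "will be employed to compare parameters at the beginning and the end of the study between and within groups, respectively". If they do not, Mann-Whitney U and Wilcoxon signed-rank tests take over. That sentence opens "For abnormal distributions data (e.g., quality of life, inflammation markers", so these outcomes are given as examples of the rank-test route.
- **ANCOVA.** When efficacy is evaluated, "center and disease will be used as covariates", and "Covariance analysis (ANCOVA) will be used". The word disease is not defined.

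On data collection, the Study design section states "All interested outcomes including patient-reported outcomes will be collected before (0 weeks) and after intervention", so a week-0 value exists for each of these outcomes.

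**The concern.** Three things are left unsettled by text that does name the tests:

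1. Which of the two routes is the main between-group analysis.
2. Whether the t or Mann-Whitney test is applied to week-12 values or to change from baseline.
3. Whether the baseline value of the outcome enters any model. Only centre and disease are named.

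The article hypothesises superiority on quality of life and inflammatory mediators (Hypothesis and objective), so these comparisons will carry claims. If the unadjusted tests are the main analysis, the trial gives up precision that its own baseline measurements would provide. With two routes and P < 0.05 applied to all analyses, the choice between them could also be made after the results are seen. A normality test on the trial data moves the comparison between a difference in means and a rank comparison, so what is estimated can depend on a preliminary test.

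**Working it through.** **Inputs from the article.** 54 per group before dropout and 60 after; 1:1 allocation; two-sided 0.05. Dropout check: 54/(1 − 0.10) = 60, as stated. The 54 is for a binary outcome (79% versus 41%) and plays no part in what follows. The article gives no standard deviation, effect size or correlation for IBDQ or the markers, so there is no planned figure to reproduce for these outcomes.

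**Assumptions.** Correlation ρ between baseline and week 12 of 0.3, 0.5 or 0.7; equal variance at both times; an approximately linear relation on the analysis scale; for the power figures, an effect of 0.5 SD with 54 evaluable per arm.

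**Variance of the treatment contrast, relative to a week-12 t test (= 1).**

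- Change-score t test: 2(1 − ρ)
- ANCOVA with baseline: 1 − ρ²
- ANCOVA relative to change: (1 − ρ²)/[2(1 − ρ)] = (1 + ρ)/2

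| ρ | Change | ANCOVA | ANCOVA / change |
|---|---|---|---|
| 0.3 | 1.40 | 0.91 | 0.65 |
| 0.5 | 1.00 | 0.75 | 0.75 |
| 0.7 | 0.60 | 0.51 | 0.85 |

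The saving is therefore 9%, 25% or 49% against week-12 values, and 35%, 25% or 15% against change. Expressed as patients, a week-12 t test would need 60/(1 − ρ²) = 66, 80 or 118 per arm to match ANCOVA with 60.

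**Detectable effect at 80% power, 54 per arm.** (1.96 + 0.842) × √(2f/54), where f is the relative variance. Week-12 t test (f = 1): 0.539 SD. ANCOVA: 0.514, 0.467 and 0.385 SD.

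**Power at 0.5 SD, 54 per arm.** Φ(0.5/√(2f/54) − 1.96). For f = 1: 0.5/0.1925 = 2.598, less 1.96 = 0.638, giving 73.8%.

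| ρ | Week-12 t | Change t | ANCOVA |
|---|---|---|---|
| 0.3 | 73.8% | 59.3% | 77.7% |
| 0.5 | 73.8% | 73.8% | 85.1% |
| 0.7 | 73.8% | 91.8% | 95.3% |

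**The rank test.** The article points these outcomes towards Mann-Whitney, so the t-test ratios do not measure that route directly. A simulation with normal data and the same assumptions (4,000 runs per correlation) gave:

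| ρ | Mann-Whitney, week 12 | Mann-Whitney, change | ANCOVA |
|---|---|---|---|
| 0.3 | 70.0% | 56.1% | 75.3% |
| 0.5 | 71.6% | 70.0% | 83.6% |
| 0.7 | 71.0% | 89.5% | 94.4% |

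Under these assumptions the ordering is the same on every reading: baseline ANCOVA is the more precise. The simulation used normal data, so it does not quantify the gain for skewed markers left untransformed.

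**The case against.** Several stronger readings are tempting, and the article does not support them.

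- **That the baseline is discarded.** A reader might infer that groups are compared on end-of-study values alone. The text refers to both the beginning and the end of the study, and the Outcomes section speaks of improvements in the markers, so change from baseline is equally possible. A change score uses the baseline, though less efficiently than ANCOVA at these correlations.
- **That there is no covariate adjustment.** ANCOVA is provided. Because disease is undefined, it might include baseline severity. It can be said only that the outcome's own baseline value is not named. If disease captures part of that value, the gain over the planned ANCOVA is smaller than the ratios above.
- **That the test for these outcomes is wholly open.** Quality of life and inflammation markers are given in advance as examples of the rank-test route. Some ambiguity remains: biochemical parameters are listed for normality testing, and the Data collecting and follow-up section counts fecal calprotectin, hs-CRP and ESR among them.
- **That results would be biased.** Under randomisation the unadjusted comparison is valid, and its standard error already allows for chance baseline imbalance. The loss is efficiency.
- **That within-group tests will be offered as proof of efficacy.** The article includes such tests but never says this.

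It is also fair to say that the covariate list for secondary outcomes often belongs in the statistical analysis plan, to which the article refers and which is not shown. That would answer a point resting on missing detail alone. Here, however, the article itself names the tests and the covariates, and gives two routes without ranking them.

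**Conclusion.** The point stands as an unranked pair of between-group analyses for the continuous secondary outcomes, with no mention of each outcome's baseline value as a covariate although it is measured. Its size depends on a correlation the article does not give. Over 0.3 to 0.7, and with an approximately linear relation, baseline ANCOVA has 91% to 51% of the variance of a week-12 t test, or 65% to 85% of that of a change-score t test. At the low end against week-12 values the gain is modest (9%); the equivalent of 118 patients per arm applies only at 0.7. The change should be made because it improves precision at no cost in data and settles the main analysis in advance. The binary primary outcome and the sample size of 60 per group do not depend on it.

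**What to change.** State one main between-group analysis for IBDQ, fecal calprotectin, TNF-α, hs-CRP and ESR: ANCOVA of the week-12 value with treatment, the baseline value of the same outcome, and site. Site belongs in the model because randomisation was stratified by it. Analyse skewed markers on the log scale, at baseline and at week 12. Report the adjusted difference, or the ratio of geometric means, with its 95% confidence interval.

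Remove the Kolmogorov-Smirnov switch, keep Mann-Whitney as a sensitivity analysis, and label within-group tests as descriptive. If a disease covariate is retained, define it.

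The cost is wording in the protocol and the statistical analysis plan. No new data are needed, since baseline values are already collected. The Trial status section describes the trial as still enrolling; on that footing the change can be fixed before database lock and unblinding.
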